### Blood samples

Daily blood samples will be obtained daily until discharge as described below. Additional blood will be obtained daily which will be processed within 1 h after collection by centrifugation at 2500 RPM or 10 min at 4 °C, and the supernatant thereof will be separated. This will thereafter be stored at − 80 °C for later examination of cytokines and complement factors at the Immunological institute, Oslo University Hospital, Norway. A fraction of the included patients will be selected for analysis of inflammatory markers in the frozen serum and microdialysate. .

### Abdominal drain fluid

Measurements of amylase activity and bilirubin from abdominal drains will be performed postoperatively in all patients.

### Patient-reported outcome measures

We will collect two self-report questionnaires. The patient questionnaire “Abdominal surgery impact scale” will be collected together with a self-reported McGill Pain Questionnaire-2 (SF-MPQ-2) preoperatively, at POD 3, at discharge, and then at POD 30 and 90. The Abdominal Surgery Impact Scale was translated into Norwegian according to the forward and backward translation method used by Tsang et al. [29].

### Assessment and management of patient based on microdialysis results

All patients in the intervention group with microdialysis glycerol > 400 μmol/ L during the first 48 h in three consecutive samples in the microdialysate will have an abdominal CT scan on POD 2. This examination will be reviewed by two senior radiologists allocated to this study and assessed according to the preexisting definitions of an abscess or radiologically visible anastomotic disruption. In the case of positive radiological findings, a subsequent CT scan will be performed according to algorithm (Fig. 1) and is described below. In the case where there is a clinical suspicion of an anastomotic leakage regardless of microdialysate values, an abdominal CT scan may be performed at the discretion of the surgeon at any time during the hospital stay, independent of microdialysate values. The CT scan will initially be assessed by the surgeon and the radiologist on call, but will also later be assessed independently by the two radiologists assigned to this study.

**Fig. 1 Fig1:**
[figure not shown]
Algorithm for assessment of patients with microdialysis. Postoperative treatment algorithm - Assessment and management of patient based on microdialysis results. CT, computer tomography; ICU, intensive care unit; L, liter; POD, postoperative day

Assessment of glycerol, lactate, and pyruvate concentration is done by the surgeon.
If the glycerol level is ≥ 400 μmol/l in 3 consecutive samples at POD1, the abdominal drain is kept to POD 2, and a CT scan is performed. If a leakage is confirmed, treatment is initiated in the following manner:

Consider
Optimizing the location of the abdominal drain and/orInsertion of a second abdominal drain and/orRelaparotomyIV antibioticsOther therapeutic actionsTransferring the patient to a higher level of care

The patient will be further assessed with clinical signs, measurement of abdominal drain output, and microdialysis values. A repeat CT (or ultrasound/ MRI) scan later in the course will be performed if the microdialysate lactate-to-pyruvate ratio is ≥ 50 combined with a lactate ≥ 4 mmol/L in 3 consecutive samples (irrespective of the time since end of surgery. If a leakage is diagnosed, the treatment described above is initiated. A repeat CT scan in a patient diagnosed with a leakage is performed on the basis of new microdialysis values (both absolute levels, and the trends thereof), the clinical condition of the patient, amylase activities, and bilirubin measured in abdominal drains.

The decision to perform a new scan and how often this will be appropriate is an interdisciplinary assessment between the surgeons and the anesthesiologist. Abdominal drains are removed later in the course if microdialysate lactate-to-pyruvate ratio is < 50, combined with a lactate < 4 mmol/L in three consecutive samples and there is no other reason to postpone their cessation (no signs of bile, chylous or enteric stained fluid and/or at the surgeon’s discretion).
b)If glycerol is persistently < 400 μmol/l within the first 24 h the abdominal drains are removed at POD 1 (prerequisite: if no signs of bile, chylous or enteric stained fluid or at the surgeon’s discretion). After this, the patients are assessed and microdialysate results are reviewed. If microdialysate glycerol is persistently < 400 μmol/l over several PODs and the lactate-to-pyruvate ratio is < 50 combined with a lactate < 4 mmol/L, the patient is further mobilized and subsequently discharged. If the glycerol increases ≥ 400 μmol/l in 3 consecutive samples at a later stage, the patient is examined, and CT scan (or ultrasound/MRI) is performed (at the discretion of the surgeon). Further intervention undertaken will be as described above.

To improve adherence to the intervention protocols, the researchers arranged an introductory- and regular follow-up meetings with the surgical team during the ongoing trial. An allocated researcher was assigned for the daily contact with the surgical team. Study newsletters and bedside training for the ward nurses were regular events during the ongoing trial. To ensure participant adherence, the patients received daily follow-up by the research team during the hospital stay, and subsequently by telephone interview at 30 and 90 days after surgery.

### Data monitoring

Monitoring the study will ensure the quality of the clinical investigation and will be performed in the MINIMUM study. The study will be monitored by “The Clinical Trials Unit,” an independent entity to the sponsor. “Monitoring” means that eCRFs will be audited to make sure that they have been completed, correctly registered and that the data are within expected values. If there are any elements of uncertainty, discrepancies in the data, missing data, or any errors are detected, the monitor will add queries into the eCRF, addressed to the investigator responsible for the patients. The monitor will track and follow these queries in cooperation with the local investigator and PI until a resolution of these queries is achieved. The monitor will use 4 days of monitoring during the study period.

### Statistical considerations

The following assumptions underlie the sample size calculations
The distribution of the primary endpoint is according to Pratt et al. [9]The effect of the intervention is measured as a reduction in median time in total hospital stay

With data collected from 35 patients undergoing the same procedure at Oslo university hospital and the median LOS in these patients, and with an assumed left censoring at 4 days (assuming that it is not possible with an admission length of less than 4 days), Weibull estimates and Log-logistic estimates were performed. A plot with the different models together with the empirical cumulative probability plot was designed and the Log-logistic model gave the best fit. However, the fit is best for the observations with short LOS, while the fit in the tail was not so good. A slight shift of 0.5 in the shape parameter gave a better fit in the tail. With the heavier tail log-logistic distribution and a reduction in median time to discharge of a clinical realistic 1.5 days, a simulation analysis with 4000 draws gave the following result:

**Table Taba:** 

Efficacy	Power	Sample size per group
-1 day(s)	0.818	155
-1 day(s)	0.909	202
-1.5 day(s)	0.814	58
-1.5 day(s)	0.932	84

In the MINIMUM study, we assume a reduction in total hospital stay ~ 1.5 days. With a significance of 0.05 and a power of 0.93, we will randomize 100 patients in each group considering that ~ 15% of the patients will not have a pancreaticoduodenectomy performed. If this number appears to be higher than the first estimate, the sample size needs to be recalculated.

The statistical analysis plan will be developed and finalized before database lock and will describe the participant populations to be included in the analyses, along with procedures for the accounting of missing, unused, and spurious data. The statistical analysis plan will be developed partly using blinded data to check for assumptions. Blinding is obtained by exchanging the treatment variable with a random allocation variable prior to any results. No unblinded analyses will be performed prior to the finalization of the statistical report. The primary endpoint will be analyzed using a log-logistic regression model with the treatment group as covariate. Results from the model will be presented as the difference in median time in hospital LOS, with 95% confidence intervals. Deaths will be imputed with worst outcome. Secondary dichotomous endpoints will be analyzed using logistic regression with the treatment group as covariate. Results from the model will be presented as odds ratios with 95% confidence intervals. Missing data will be imputed with worst outcome. Secondary continuous endpoints will be analyzed using linear regression for non-repeated measures or mixed effects linear regression for repeated measures. Generalized linear model versions or quantile regression models will be considered if the assumptions underlying the normal linear model are assumed to be violated based on blinded analyses. Treatment differences will be presented with 95% confidence intervals. Time to event endpoints will be analyzed using competing risk methodology, with the event and death as competing risks. Results from the model will be presented as hazard ratios with 95% confidence intervals.

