### Objectives and endpoints

Our primary objective is to evaluate if the microdialysis method will reduce the total LOS at the hospital in patients undergoing pancreatoduodenectomy. The primary and secondary objectives combined with the primary, secondary, and other explorative endpoints and how they are assessed are presented in Table 1.

**Table 1 Tab1:** Primary and secondary objective. Primary, secondary, and other explorative endpoints and how they are assessed

Objectives		Endpoints	Assessments
Primary	To evaluate if the microdialysis method will reduce the total length of stay at the hospital(s).	Number of days/hours from end of surgery to hospital discharge from primary hospital plus number of days/hours for subsequent admissions with a diagnosis associated with the primary surgery at any hospital	Hours/days from the initial operation (end of surgery) to hospital discharge. All hospitals admitting the patient are included, also transferred hospitals. From electronic patient records.
Secondary 1	To evaluate predictive score systems for POPF	Occurrence of POPF	POPF defined according to the definition of the ISGPF. Graded into “biochemical”, B or C. From medical record, CT-scans. The following risk factors will be assessed: Age, gender, smoking history—current and package years, preoperative BMI, weight loss, Intraabdominal fat thickness, pancreatitis history, relation to portal vein to tumor, primary diagnosis, radiological (assessed by CT-scan) PD width, intraoperative PD width, intraoperative blood loss, pancreatic texture, pancreatic fat, pancreatic fibrosis, drain amylase. From preoperative examination, medical record, CT-scan, during surgery and postoperative examinations.
Secondary 2	To evaluate if microdialysis data contribute to reduced length of stay at the primary hospital and ICU	Length of stay at the primary hospital Length of stay at the ICU	Number of days/hours from end of initial operation to primary hospital discharge and hours admitted at the ICU. From electronic patient records.
Secondary 3	To evaluate if there is a special pattern of inflammatory markers in the microdialysate and serum in patients with/without POPF	Concentration of inflammatory markers	From laboratory analysis

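### The primary log-logistic model names treatment as its only covariate, although likely prognostic factors are recorded before randomisation; prespecified adjustment would add some precision at little cost

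*Protocol article*

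**What the plan says.** Statistical considerations fixes the primary model and its effect measure: "The primary endpoint will be analyzed using a log-logistic regression model with the treatment group as covariate", and "Results from the model will be presented as the difference in median time in hospital LOS, with 95% confidence intervals". Treatment group is the only covariate named.

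The design behind this is a median reduction of 1.5 days: "In the MINIMUM study, we assume a reduction in total hospital stay ~ 1.5 days". The sample size follows: "With a significance of 0.05 and a power of 0.93, we will randomize 100 patients in each group". The table row it rests on reads "1.5 day(s) 0.932 84", that is, power 0.932 with 84 per group, before an allowance of about 15% for patients in whom the operation is not carried out.

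On the data available, Table 1 (Secondary 1) introduces its list with "The following risk factors will be assessed: Age, gender, smoking history". The list goes on to preoperative BMI, primary diagnosis and duct width on CT, among others. In the assessment schedule (Table 2), age and BMI stand in the pre-admission column, duct width from the preoperative CT in the pre-operative column, and randomisation in the intra-operative column.

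**The concern.** Length of stay varies widely between patients, and part of that variation can probably be predicted before surgery. The trial's own reasoning points to likely predictors. The background says that postoperative morbidity prolongs stay, the hypothesis is that earlier detection of a pancreatic fistula shortens it, and Table 1 lists patient and pancreas characteristics as fistula risk factors. A model with treatment alone leaves whatever these factors explain in the residual variance. The confidence interval for the primary comparison is then wider than the collected data require.

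This is a choice that the article states, not a gap in it. The model, its covariate and its effect measure are all named, so it is fair to ask whether a better use of data already in the case report form is available. What is at stake is some width of the interval and a few points of power.

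**Working it through.** **Inputs from the protocol article.** Power table: 0.818 at 155 and 0.909 at 202 per group for a 1-day reduction; 0.814 at 58 and 0.932 at 84 for 1.5 days. Loss about 15%. Significance 0.05; two-sided is assumed, in line with the 95% interval. The median and shape of the simulated log-logistic distribution are not given.

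**Input assumed.** R², the share of the variance of log stay explained by baseline covariates: 0.05, 0.10 or 0.20. The documents give no value.

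**Step 1: reproduce the plan's figures.**
- Loss: 84 / (1 − 0.15) = 98.8, so 99 per group against 100 stated.
- Standardised effect = (1.960 + z_power) / √(n/2). The two 1.5-day rows give 0.530 and 0.533; the two 1-day rows give 0.326 and 0.328.
- The 58-per-group row predicts power at 84 of Φ(0.5297 × √42 − 1.960) = 0.930, against 0.932 stated. The 155 row predicts 0.906 at 202, against 0.909 stated.
- A log-logistic model calibrated to the table (implied median about 4.2 days above the 4-day limit, shape about 2.1), fitted with treatment only in 1,500 simulated trials per row, gave 0.817, 0.913, 0.825 and 0.931. The stated values are 0.818, 0.909, 0.814 and 0.932.

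The stated design is therefore internally consistent for the unadjusted analysis.

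**Step 2: effect of adjustment at 84 per group, 1.5 days.** Power of 0.932 corresponds to 1.960 + 1.491 = 3.451 standard errors. Adjustment multiplies the residual variance by (1 − R²), so power = Φ(3.451/√(1 − R²) − 1.960), and the interval width is multiplied by √(1 − R²):

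| R² (assumed) | Power | Width factor | n per group for the same power, 84 × (1 − R²) |
|---|---|---|---|
| 0 | 0.932 | 1 | 84 |
| 0.05 | Φ(1.581) = 0.943 | 0.975 | 79.8 |
| 0.10 | Φ(1.678) = 0.953 | 0.949 | 75.6 |
| 0.20 | Φ(1.898) = 0.971 | 0.894 | 67.2 |

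The width factor belongs to the treatment coefficient on the log-time scale; for the difference in days it is approximate.

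**Step 3: check by simulation.** With the calibrated model and one baseline covariate, power without and with adjustment was 0.916 and 0.944 (R² = 0.10), and 0.915 and 0.971 (R² = 0.20). The adjusted figures agree with the formula to within about 0.01.

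**Step 4: the smaller effect in the protocol's own table.** For a 1-day reduction, using the mean standardised effect of 0.327, power at 84 per group is Φ(0.327 × √42 − 1.960) = 0.56. It becomes 0.58, 0.61 and 0.66 for R² of 0.05, 0.10 and 0.20.

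**The case against.** The strongest reply is that nothing is wrong with the plan. A treatment-only comparison is valid under 1:1 randomisation, it matches the model family used for the sample size, and it reaches the stated power without adjustment. The article names no stratification factors that the model would have to carry. All of this stands.

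It is also fair that every R² above is assumed. A reader might call the collected factors strong predictors of stay, but the documents do not show that. They are listed for an objective that evaluates predictive scores for fistula, so their value is itself under study, and no figure links any of them to length of stay.

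A reader might also infer that the preoperative quality-of-life and pain scores go unused. The article does not say so. The questionnaires are collected "preoperatively, at POD 3, at discharge, and then at POD 30 and 90", and the model statement is "Secondary continuous endpoints will be analyzed using linear regression for non-repeated measures or mixed effects linear regression for repeated measures". It lists no covariates, and a mixed model can take the preoperative score as a covariate or as the first repeated measure. That detail is commonly left to the statistical analysis plan and is no finding.

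Finally, a reader might argue that chance imbalance in these factors could distort the result. The design implies a standard error of 1.5 / 3.451 = 0.43 days. The part due to imbalance has standard deviation √R² × 0.43, about 0.10, 0.14 and 0.19 days for R² of 0.05, 0.10 and 0.20. The unadjusted interval already allows for this.

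What the reply does not remove is that the article fixes a model which sets aside pre-randomisation information already being collected.

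**Conclusion.** The point holds as an efficiency improvement to a stated analysis choice. It is not an error, there is no bias, and the sample size needs no correction. For an assumed R² of 0.05 to 0.20, the gain is about 1 to 4 points of power at the design effect and an interval narrower by about 2.5% to 11%. If the true reduction is 1 day, the gain is about 2 to 10 points on a power of 0.56. The direction is dependable if the covariates are prognostic; the size cannot be derived from the documents. If the covariates explained almost nothing, the loss from fitting three or four of them in about 170 patients would be negligible.

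**What to change.** Before any unblinded analysis, prespecify the primary analysis as the log-logistic model with treatment plus a few covariates recorded before randomisation:

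- preoperative CT pancreatic duct width, BMI and age;
- preoperative working diagnosis, only if it is confirmed to be recorded before allocation. Table 2 describes current diseases through histology and staging, so its timing is unclear;
- not postoperative histology and not drain amylase, which arise after allocation.

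State the functional form of each covariate and how a missing baseline value is handled. To keep the promised effect measure, average the fitted curves over all patients under each allocation, read off the two medians, and report their difference with a delta-method or bootstrap 95% confidence interval. Keep the treatment-only model as a sensitivity analysis.

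The cost is wording in the analysis plan and moderate extra programming for the standardised median difference and its interval. No new data, visits or patients are needed. The article says that the plan is finalised before database lock, so the change can still be made without knowledge of the treatment effect.

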**Methods:**

The MINIMUM study is a prospective, randomized, controlled, single center enrolling 200 patients scheduled for open pancreatoduodenectomy comparing the microdialysis method to the “standard of care.” Half of the included patients will be randomized to receive an intraperitoneal microdialysis catheter implanted at the end of surgery and will be monitored by microdialysis as an additional monitoring tool. The other half of the patients will not receive a microdialysis catheter and will be monitored according to the current standard of care. The primary objective is to evaluate if the microdialysis method can reduce the total length of stay at the hospital. Secondary endpoints are the frequency of complications, length of stay at the hospital at our institution, catheter malfunction, number of infections and bleeding episodes caused by the microdialysis catheter, patient-reported quality of life and pain, and cost per patient undergoing pancreatoduodenectomy. The patients will be randomized in a 1:1 ratio.

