Secondary 4	To evaluate the reliability and complications using microdialysis catheter CMA 65	Occurrence of catheter malfunction Occurrence of bleedings and infections	Daily check of the microdialysis catheter is functioning. Assessments of bleeding which affects circulatory parameter (development of circulatory shock or need of transfusion) and infection
Secondary 5	To evaluate patient quality of life and pain	Overall score and sub-scale scores of patient-reported questionnaires	Two patient-reported questionnaires: “Abdominal surgery impact scale” will be gathered with patient-reported McGill Pain Questionnaire-2 (SF-MPQ-2) preoperatively, at POD3 ± 1 day and at discharge ± 2 days from primary hospital + 30 and 90 days after surgery.
Secondary 6	To compare hospital costs of using microdialysisis versus “standard of care”	Number of Euros per patient undergoing PD based on microdialysis costs, length of stay (ICU and inpatient stay), reoperations, and postoperative complications	From medical records, procedures noted in electronic patient records, and radiological electronic patient records.
Exploratory	To compare other endpoints between patient with and without a microdialysis catheter	Hours from end of surgery to diagnosis of postoperative pancreatic AL (grades B and C).	Time as noted in electronic patient records.
		Total quantity (μg/mg) of vasoactive medications during surgery	Amount during surgery where the PD was performed. Derived from electronic patient records.
		Fluid balance - total iv volume administered and total diuresis	Diuresis and amount of fluid given iv during surgery and postoperatively until discharge from the hospital where the PD was performed. Derived from electronic patient records.
		Number of patients with biliary fistula	Biliary fistula defined according to the definition of the International Study Group of Liver Surgery (ISGLS). Graded into A, B, or C. From medical record, CT-scans.
		Number of patients with gastro-enteric AL	Gastro-enteric AL. From medical record, CT-scans.
		Pancreatic amylase and bilirubin concentrations in drainage fluid and in serum.	Analysis of drainage fluid and serum
		White blood cell count, C-reactive protein; concentrations	Laboratory data
		Number of patients with postoperative complications during total hospital stay in total and per complication	Defined by the modified Clavien-Dindo classification, from medical record, radiological examinations, and electronic patient records.

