### Design, enrollment, inclusion, and randomization

The MINIMUM study is a 2-armed, single-center, randomized, parallel-group trial with an equivalence framework. The study population is patients scheduled for open pancreatoduodenectomy at Oslo University Hospital – Rikshospitalet, Norway. This center normally performs 130 open pancreatoduodenectomy each year and MINIMUM seeks to enroll 200 consecutive patients scheduled for open pancreatoduodenectomy. Half of the included patients (intervention group) will be randomized to receive an intraperitoneal microdialysis catheter inserted at the end of surgery and will postoperatively be monitored by microdialysis. The surgeon will have full access to the microdialysis results at any time during the study period. The surgeon may intervene based solely on the patient’s symptoms and signs, plus predetermined values of the microdialysis measurements. The other half of the patients (control group) will not receive a microdialysis catheter. The patients are monitored according to the current standard of care and the surgeon may intervene based only on symptoms and signs. The only difference between the two groups is that the treating surgeon in the intervention group will implant a microdialysis catheter close to the pancreaticoenterostomy. Once implanted, the microdialysis results will be available to the treating team, and these results can be included into the assessment and management of the patient. Group assignments will be determined by an online randomization system; (Viedoc™) developed by PCG Solutions ([name]). Screening and enrollment of patients will be performed by the investigators. All the patients will be included minimum 1 day prior to surgery. The study will be conducted according to the Helsinki declaration. A special combined patient information leaflet and consent form has been developed for the MINIMUM study. Patients will be recruited from the operation planning program on site. After informed consent has been obtained by the principal investigator or co-investigator, the patients will be included. The trial will be conducted in accordance with the Consolidated Standards of Reporting Trials (CONSORT) Statement.

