**Histological assessment**							
**Pancreatic fat**			X				
**Pancreatic fibrosis**			X				
**Drain tube**			Insertion	Cessation POD 1–3 (or more) unless the effluent is bile, enteric stained or turbid or depending on microdialysis concentrations			
**Amylase and bilirubin in drain fluid**				At POD 1–3 and on indication thereafter if drain still in place			
**Pantoperazole 40 mg iv**				Administered daily for 7 days			
**Sampling/analyzing microdialysate**				Every hour in the first 24 h. Thereafter, every two hours until POD 2. From POD 2: every 4th hour until discharge; Pyruvate, lactate, glucose, glycerol			
**Collecting microdialysate for cytokines**				Twice daily (≈ 08.00 am and 08.00 pm)			
**Microdialysis catheter function and duration**			X	X			
**Abdominal CT scan during admission(s)**				POD 2 in patient with high microdialysate concentrations in three consecutive microdialysate samples and/or at the surgeon's discretion	at the surgeons discretion	at the surgeons discretion	at the surgeons discretion
**Postoperative complications - Clavien-Dindo classification ≥ 2**				X	X	X	X
**Time from end of surgery to a diagnosed anastomosis leakage, if applicable**				X	X	X	X
**Type of complications**				X	X	X	X
**Type of procedures due to complications**				X	X	X	X
**Cost of complications**				X	X	X	X
**Transfer(s) to ICU**				X	X	X	X
**LOS at primary hospital and ICU**				X	X	X	X
**LOS at secondary hospital**						X	X
**Mortality**			X	X	X	X	X

*ALAT* alanine aminotransferase, *ALP* alkaline phosphatase, *ASAT* aspartate aminotransferase, *BMI* body mass index, *CRP* c*-*reactive protein, *CT* computed tomography, *GFR* glomerular filtration rate, *GGT* gamma*-*glutamyl transferase, *Hb* hemoglobin, *ICU* intensive care unit, *LD* lactate dehydrogenase, *LOS* length of stay, *PBW* predicted body weight, *PD* pancreatic duct, *POD* postoperative day, *SpO2* peripheral oxygen saturation, *TNM* tumor-nodule-metastasis, *Trc* platelets, *WBC* white blood cells

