### Microdialysis catheter and microdialysis analysis

Our research group has previously shown that microdialysis catheters with pore size for particles up to 100 kDa collect cytokines and complement factors, consequently, CMA 65 is used in this study [28]. The catheter is flexible and allows for the continuous monitoring and detection of local metabolic changes in the gastrointestinal tract. The catheter has a shaft length of 180 mm with a 30 mm membrane made of polyarylethersulfone. The diameter is 0.9 mm. The microdialysis catheter is tested for functionality before implantation. Before skin closure, the catheters will be implanted through a percutaneous hypodermic needle and affixed with an absorbable suture to surrounding connective tissue in close vicinity (< 1 cm) to the pancreaticojejunostomy. An epidermal suture will be used to minimize the risk of unintentional dislodgement. The catheters will be kept until the patient is discharged from the primary hospital or the catheter malfunctions.

The catheter is connected to a small battery-driven syringe pump (CMA 107, M Dialysis AB) and perfused by hydroxyethyl starch solution 130/0.4 (Voluven®, Fresenius Kabi AS, Halden, Norway) pumped at a rate of 1 μL/min as dialysis solution. The microdialysate will be collected in microvials which will be changed and analyzed hourly for metabolic parameters and cytokines. The samples thereafter will be analyzed for lactate, pyruvate, glucose, and glycerol with ISCUSflex Microdialysis Analyzer® (M Dialysis AB, Johanneshov, Sweden) by trained nurses/physicians in the following manner:
Every hour for the first 24 h.Thereafter, every 2 h as long as the microdialysis catheter still functions. With the exception of the initial 24 h, nighttime samples will be done at 0.00, 4.00, and 8.00 am.After POD 2 at 0.00 am: If the lactate/pyruvate-ratio increases > 50 combined with lactate > 4 mmol/L AND/OR glycerol increases > 400 μmol/L, the next two samples will be performed with an interval of 2 h (in place of every 4 h at night) to confirm or refute a pathological process.

Twice daily (≈ 08.00 am and 08.00 pm), samples from the microvials will be kept, and frozen to − 80 °C for later examination of cytokines and complement factors.

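### As written, the default logistic rule gives no estimable odds ratio for catheter malfunction, because controls have no catheter; analyse it in catheter recipients with time at risk

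*Protocol article*

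**What the plan says.** Table 1 of the protocol article gives Secondary 4 the objective "To evaluate the reliability and complications using microdialysis catheter CMA 65", with "Occurrence of catheter malfunction" as its first endpoint. The abstract also lists malfunction among the secondary endpoints.

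Under Statistical considerations, models are assigned by endpoint type. For yes/no endpoints, "Secondary dichotomous endpoints will be analyzed using logistic regression with the treatment group as covariate", and "Results from the model will be presented as odds ratios with 95% confidence intervals". The next sentence sets missing data to the worst outcome. No endpoint is excepted.

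Under Design, enrollment, inclusion, and randomization: "The other half of the patients (control group) will not receive a microdialysis catheter".

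On how long the device stays in place, the section on the microdialysis catheter says: "The catheters will be kept until the patient is discharged from the primary hospital or the catheter malfunctions". Table 2 schedules the recording of "Microdialysis catheter function and duration", but no rule under Statistical considerations uses that duration for this endpoint.

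**The concern.** A regression on treatment group compares two arms. Malfunction can occur in only one of them, so the zero in the control arm follows from the design and is not a sparse-data accident. The specified odds ratio therefore cannot carry information on whether the catheter is reliable. If control values were coded as missing, the worst-outcome rule would count patients without a catheter as malfunctions.

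The obvious fallback, the share of catheter patients with a malfunction, can be calculated but has two limits. Time at risk ends at primary-hospital discharge, so the share rises with length of stay even when the device is equally reliable. It also treats all failures alike. The protocol's algorithm uses glycerol in the first 24 h for the drain decision and in the first 48 h for the POD 2 CT scan, and later values for surveillance. A failure inside the early windows removes the information those decisions rely on; a failure late in a long stay has a different meaning.

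**Working it through.** **Step 1. Which stated rule applies.** Occurrence of malfunction is a yes/no secondary endpoint, so by type it falls under the logistic rule. The time-to-event rule would not rescue it. That rule reports hazard ratios, which between groups meet the same empty arm, and it names death but not discharge as a competing event.

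**Step 2. Denominator.** The plan's table gives 84 per group, with about 15% expected not to have the operation: 84 / (1 − 0.15) = 98.8, or 99, in line with the stated 100 per group. Patients at risk in the catheter arm: 100 × 0.85 = 85. The documents give no malfunction rate, so the counts below are assumptions.

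**Step 3. The specified odds ratio.** With *a* malfunctions among 85 catheter patients and 0 among 85 controls, OR = [*a*/(85 − *a*)] / [0/85], which has no finite value. A binomial GLM with a logit link was stopped after 10, 20 and 30 iterations. The table also shows the odds ratio after adding 0.5 to each cell, (*a* + 0.5)(85.5) / [(85.5 − *a*)(0.5)], and the catheter-arm proportion with its exact (Clopper-Pearson) interval.

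| Assumed *a* | Log OR at 10 / 20 / 30 iterations | OR with 0.5 added | Catheter-arm proportion (95% CI) |
|---|---|---|---|
| 5 | 8.8 / 18.8 / 28.8 | 11.7 | 5.9% (1.9% to 13.2%) |
| 10 | 9.6 / 19.6 / 29.6 | 23.8 | 11.8% (5.8% to 20.6%) |
| 20 | 10.4 / 20.4 / 30.4 | 53.5 | 23.5% (15.0% to 34.0%) |
| 30 | 11.0 / 21.0 / 31.0 | 94.0 | 35.3% (25.2% to 46.4%) |

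The standard error grows from about 21 to 3,171 to over 470,000, so the fit never converges. The corrected odds ratios reflect the structural zero in controls, not reliability. The last column shows that a one-arm estimate is available.

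**Step 4. Dependence on stay.** With a constant daily hazard *h* (assumed) and a catheter left in for *d* days, the proportion failing is 1 − exp(−*hd*).

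| *h* per day | 5 days | 7 days | 14 days | 21 days | Ratio, 21 to 5 days |
|---|---|---|---|---|---|
| 0.03 | 14% | 19% | 34% | 47% | 3.4 |
| 0.05 | 22% | 30% | 50% | 65% | 2.9 |
| 0.10 | 39% | 50% | 75% | 88% | 2.2 |

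These are contrasts between individual stays. A simulation for a whole arm is milder. Stays were log-logistic with a 4-day minimum and scale 0.5, capped at 90 days, with assumed medians of 8, 10 and 12 days. The crude share was 17.5%, 21.6% and 25.2% at 0.02 per day; 36.8%, 43.3% and 48.7% at 0.05; and 58.0%, 65.1% and 70.5% at 0.10. Malfunctions divided by catheter-days returned the true hazard (0.020, 0.050, 0.100) at all three medians.

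**Step 5. Fixed early times.** The proportion still functioning at time *t* is exp(−*ht*). At 24 h it is 97.0%, 95.1% and 90.5% for *h* = 0.03, 0.05 and 0.10; at 48 h it is 94.2%, 90.5% and 81.9%. These do not change with the stay as long as patients remain in hospital that long. The sample-size section assumes that no admission is shorter than 4 days.

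**The case against.** The strongest reply is that the logistic sentence is a generic default for treatment comparisons and never names malfunction. Several secondary objectives are plainly not arm comparisons: Secondary 1 concerns scores that predict fistula, and Secondary 3 concerns marker patterns by fistula status. Secondary 4 speaks of evaluating one named catheter, which reads naturally as a one-arm description. The protocol also leaves analysis populations to a statistical analysis plan that is not shown. This has weight: the team may well intend a one-arm summary. It does not remove the point, because the text states a contrast and an effect measure for all yes/no secondary endpoints. Defining a population does not change that contrast.

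A reader might go further and infer that the trial cannot yield any usable estimate of reliability. The documents do not support that. Function is checked daily and duration is scheduled for recording, so a catheter-arm proportion with an interval can be read from the data. The failure is confined to the specified odds ratio.

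A reader might also infer that dependence on stay biases a treatment comparison. It does not, because no comparison of malfunction between arms is possible. The share failing before discharge is also a legitimate answer to whether the device lasted as long as it was in use. What stands is that this share cannot be read as device durability and does not show when failures occurred.

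**Conclusion.** The point holds as a minor one. That the odds ratio is not estimable needs no assumption beyond reading the logistic rule as written and noting that controls have no catheter. The dependence of the crude proportion on stay limits its interpretation. Its size is illustrative only: about 2.2- to 3.4-fold between a 5-day and a 21-day stay for hazards of 3% to 10% per day. The hazards, their constancy, the stays and the malfunction counts are all assumptions. The primary endpoint, the sample size and the safety interim analysis are not affected.

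**What to change.** State that catheter malfunction is exempt from the between-group logistic rule and that worst-outcome imputation is not applied to controls for it. Then, in patients with an implanted catheter only, and using the function and duration data already in Table 2:

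- report the proportion of catheters still functioning at 24 h and 48 h after implantation, with 95% confidence intervals;
- report malfunctions per catheter-day, or the cumulative incidence of malfunction, with 95% confidence intervals;
- let exposure end at discharge with a working catheter, at other removal, or at death;
- if wanted, give the crude proportion failing before discharge alongside, labelled as dependent on stay.

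A further time point such as POD 4 is optional. It would rest on the minimum stay assumed for the sample size and is not a decision point of the algorithm. Because discharge may itself depend on microdialysis values, later time points call for more cautious reading than the two early ones.

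The cost is a few lines of wording and a small extra descriptive analysis, with no new data collection.
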